### Participants

The objective is to recruit a minimum of 30 first-semester physiotherapy students from the BFH-SHP (17). This *a priori* set recruitment rate will be used as a criterion of success to evaluate the feasibility and the timeframe of recruitment for the upcoming fully randomized controlled higher-education study (3). The participants are young healthy adults, are enrolled at the BFH-SHP and affiliated with the bachelor physiotherapy degree cohort. Students who do not intend to participate will be excluded from the recruitment process.

The retired physiotherapists will be recruited by means of an advertisement in the official journal “physioactive” of the Swiss Physiotherapy Association and by asking colleagues. They will be informed in writing and orally about the course of the study and their participation in the study.

### Eligibility criteria

Inclusion criteria for the students are: (1) young healthy physiotherapy students, (2) enrolled at the undergraduate physiotherapy degree course 2019 (first semester) at the BFH-SHP, and (3) signed informed consent. Exclusion criteria are: (1) physiotherapy students from undergraduate physiotherapy course 2018 who needed to repeat the first semester, (2) students from other BFH-SHP degree courses, and (3) physiotherapy students from other institutions.

Inclusion criteria for retired physiotherapists are: (1) retired or still working with patients for a maximum of 10% and (2) healthy. Exclusion criteria are: (1) work more than 10% on patients or in another profession, (2) have been employed in teaching, (3) have previously supervised student interns, and (4) have cognitive impairments.

### Intervention program

A total of six G-SS cycles with six different cases will be conducted in the first semester. The intervention program aimed to investigate feasibility and impact of six G-SS sessions on changes in knowledge and skills in pre-clinical physiotherapy students at the BFH-SHP. Students of the G-SS will be divided into five groups of five to six students each. They will work on a clinical case in an 8-day cycle. The structure of the eight-day cycle will be based on Rogan et al. (3, 6, 13, 14, 18). Phase 1, day 1: students of the G-SS and the retired physiotherapists will receive on day 1 (i.e., 1 week prior to the presentation day) via email a clinical case for processing. Phase 2, day 2–7: students will be guided by their tutors during the one-week preparatory phase. Students will have the possibility to arrange two online meeting sessions with their tutor. In these meetings, questions can be answered, and the current status and stumbling blocks can be addressed and solved. Phase 3–5, day 8: students will present their findings and solutions of their work orally and practically. In a moderated plenum session students will conclude the working process and learning process, any questions and optimization steps are clarified. Feedback will be given to the students by the tutors.

The first semester includes topics and learning objectives from the module “Basics of physiotherapeutic Patient Examination.” The topics of the first semester are: basic movement, testing coordination, manual muscle strength tests, massage techniques, movements and joint position, muscle activities, palpation, passive and active angular joint examination, statics and constitution, translational joint examination and tests for muscle flexibility. The G-SS will be scheduled in the school timetable with a total workload of <40 h per week. The case topics are listed in Table 1.

**Table 1 tab1:** Topic of the cases during the G-SS cycles in the first semester.

G-SS cycle	Topic
1.	Massage technique
2.	Joint measurement, differentiation of musculature
3.	Gait analysis
4.	Joint measurement with goniometer and app for comparison
5.	Hip joint region: Examine neighboring joints
6.	Case study in context of Clinical Reasoning

### Control condition

F-SS will be scheduled during this period. Students in the control group will be given the same amount of time in the timetable for F-SS. There is no supervision nor tutoring and students will not receive a clinical case and will receive no information on the direction of what they can do.

#### Achievement characteristics

The *a priori* set criteria of success for feasibility and preliminary data for changes in knowledge and skills will be evaluated at the end of the first semester (February 2020).

#### Primary achievement goal

Criteria of success will be operationalized as “fidelity of implementation” (19), such as time of task, students’ responsiveness, and the acceptability of the intervention from the students’ perspective and the recruitment of retired physiotherapists as tutors. “Fidelity of implementation” has been described as to which level the intervention is implemented as intended by those who developed it (19, 20).

#### Measures

##### The fidelity of implementation will be assessed for

time of task as (i) participation at all six presentation days (i.e., days 8 of the cycles; phase 3–5), and (ii) the duration of the session on day 8 is limited to maximum 90 min.students’ responsiveness will be recorded by the retired physiotherapists in an attendance list on the presentation day eight. Criteria of success will be defined as at least 83% of the physiotherapy students of the G-SS taking part in five out of six presentation days (i.e., day 8 of the cycles; phase 3–5).

##### Acceptability of intervention from students’ perspective

Acceptability of G-SS will be assessed from the physiotherapy students using a questionnaire with open, semi-structured questions at the end of day 8 of the sixth G-SS cycle (post intervention). The interview protocol will obtain the students’ opinion and experiences of the G-SS.

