**Figure 1 fig1:**
[figure not shown]
Flow of the study design.

This study protocol on G-SS is based on the SPIRIT statement (16). The overall project has been approved by the cantonal ethics commission of Bern (2018–01683) and registered in the German Register of Clinical Studies (DKRS: DRKS00015518). The participation will be voluntary. Physiotherapy students can withdraw from this feasibility study at any time. Those who withdraw voluntary from the study will follow the normal curriculum. Their data will not be used for the analysis. Students will be informed both oral and written about the study design and they will sign a consent form agreeing to participate in the study.

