#### Secondary achievement goals

These include the learning outcomes, satisfaction, self-efficacy, and students’ images of old age. Physical performance level of the retired physiotherapists and the G-SS implementation into the curriculum.

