### Outcome measures

Students’ learning outcome

Students’ learning outcome could be defined as of what a learner is expected to know, understand or be able to do at the end of a period of learning (21). Learning outcome will be measured based on the semester exams (ordinal scaled) including written multiple-choice questions (MCQs) and an Objective Structured Clinical Examination (OSCE). The written exams consist of 87 single best answer MCQs. The OSCE consist of eight 8-min stations. The maximum score will be 87 and 64 points for the MCQs and OSCE, respectively. The exam will be passed if 60% of the total score is reached.Student’s satisfaction will be assessed with the student learning satisfaction questionnaire (22).Self-efficacy will be assessed using the self-efficacy learning (SEL) questionnaire (23).
Level of retired physiotherapists’ physical and cognitive performance. Physical performance capacity will be evaluated using the Short-Physical-Performance-Battery-Test while evaluation of the cognitive performance will be assessed using the Trail-Making A and B test before the start of the tutorship after the end of the first and second semester, respectively.Level of age images of physiotherapy students are assessed before the G-SS and F-SS lessons at the end of first and second semester, respectively. Age images will be assessed with the age images questionnaire (24).Level of G-SS curriculum implementation: the integration of G-SS into the existing curriculum will take place after evaluation of this planned feasibility study (i.e., after the second semester).

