### Data collection methods

The first collection of data by means of surveys is scheduled for the start of the project (T0). Thereafter, the same surveys will be filled out by the students participating in this planned feasibility study after the fall semester (T1) and after the spring semester (T2). Before-and-after learning effects will be shown in the intervention group and the control group as well as between the groups are presenting using parametric methods. If a retired physical therapist, or a physiotherapy student, does not wish to continue participating in this study, that person will, upon request immediately removed from the study program. The date of discontinuation will be noted and placed in the files or records. The data will be anonymized after the analysis.

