### Statistics

Because this study is a feasibility study, testing intervention effects is not a key part of this study design (18). Baseline descriptive statistics will be used to describe G-SS and F-SS group characteristics and to illustrate the feasibility goals. The independent variable will be G-SS. The dependent variable will be the final grades of the MCQs and OSCE. Preliminary group differences at the end of the first semester will be analyzed with the Mann–Whitney-U-Test. The significance level will be set *a priori* to *p* = 0.05. An intention-to-treat analysis will always be the primary analysis of a randomized trial in higher education (17). An ITT will be carried out if physiotherapy students do not adhere to the G-SS protocol.

The findings of the satisfaction and self-efficacy items will be summarized visually in a table and presented as response distributions (number, percentage). Satisfaction analysis will involve the summation satisfaction scale scores, with 0.80 as the proposed threshold for defining usability and acceptability, counting only positive endorsements (4 = agree, 5 = strongly agree). Qualitative data from the semi-structured interview will be analyzed thematically.

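### Acceptability, a primary feasibility goal, is asked only of students present at the sixth session, so absentees and leavers are not heard

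*Protocol article*

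**What the plan says.** The Aim and Primary achievement goal sections of the protocol article place students' acceptability among the primary feasibility goals. The section on acceptability from the students' perspective fixes a single collection: it will be assessed "using a questionnaire with open, semi-structured questions at the end of day 8 of the sixth G-SS cycle (post intervention". No other occasion is given for this form, and no numerical criterion is attached to it.

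Three other statements determine who can be heard:

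- **Measures:** responsiveness succeeds if at least 83% of G-SS students attend five of the six presentation days.
- **Study setting, after Figure 1:** of students who withdraw, "Their data will not be used for the analysis".
- **Statistics:** an intention-to-treat analysis is promised where students do not follow the G-SS programme.

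A different instrument carries the only numerical rule that mentions acceptability. Under Outcome measures, "satisfaction will be assessed with the student learning satisfaction questionnaire (22". Secondary achievement goals lists satisfaction as secondary: "These include the learning outcomes, satisfaction, self-efficacy". The Statistics section sets the rule for that questionnaire: "Satisfaction analysis will involve the summation satisfaction scale scores, with 0.80 as the proposed threshold for defining usability and acceptability". A closing clause limits which ratings enter, by "counting only positive endorsements (4 = agree, 5 = strongly agree". Data collection methods schedules surveys at the start and adds "Thereafter, the same surveys will be filled out by the students participating in this planned feasibility study after the fall semester (T1", with a further round after the spring semester.

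**The concern.** A student who found G-SS unhelpful is more likely than a satisfied one to skip the last session or to have stopped coming. Asking only those in the room at the end therefore selects on something close to the outcome itself. The intention-to-treat statement does not cure this, because an analysis rule cannot recover opinions that were never collected.

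The article says that this study is to supply what is needed to design the main study. A picture of acceptability that is too favourable would carry over into that design.

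A smaller matter is the 0.80 threshold. It is worded both as a summed scale score and as a count of ratings of 4 and 5, with no unit or denominator. The verdict on satisfaction can then depend on a reading chosen after the data are seen.

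**Working it through.** The plan derives no figure for acceptability, so there is none to reproduce. The checks below bound the possible error.

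**1. Who may be missing at session six**

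The Intervention program section gives five groups with five or six students in each, so 25 to 30 in the G-SS arm.

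- 25 students: 0.83 × 25 = 20.75, so 21 must meet the criterion and 25 − 21 = 4 need not (4/25 = 0.16).
- 30 students: 0.83 × 30 = 24.9, so 25 must meet it and 5 need not (5/30 = 0.167).
- The Sample size section has 102 students in two groups, 51 each if equal: 0.83 × 51 = 42.3, so 43 must and 8 need not (8/51 = 0.157).

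These count low attenders. They do not cap absence at session six, because a student who meets five of six may miss the sixth. If all 30 met the criterion and each missed one session, spread evenly, 30/6 = 5 would be absent from session six.

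**2. Size of the bias**

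Suppose the open answers are coded as favourable or not, which is an assumption made only for this illustration. Let r be the share of allocated students who answer, f the favourable share among them and g the unknown favourable share among the rest.

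- Share in all allocated students = r·f + (1 − r)·g
- Overstatement = f − [r·f + (1 − r)·g] = (1 − r)(f − g)

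If the 4 of 25 or 5 of 30 are the ones missing:

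| f − g (assumed) | 25 students | 30 students |
|---|---|---|
| 0 | 0 | 0 |
| 0.5 | 0.16 × 0.5 = 0.08 | 0.167 × 0.5 = 0.083 |
| 1 (worst case) | 0.16 | 0.167 |

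The documents do not say where f − g lies.

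**3. Unit of the 0.80 rule (satisfaction questionnaire only)**

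The plan counts only ratings of 4 and 5. Let E be the share of responses rated 4 or 5, and m the mean rating among those.

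- Summed positive score over maximum: S = E × m/5, with m between 4 and 5.
- So S lies between 0.8·E and E.

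Take one item and 30 students, of whom 24 rate it 4 and 6 rate it 1:

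- E = 24/30 = 0.80, which meets the threshold.
- S = (24 × 4)/(30 × 5) = 96/150 = 0.64, which does not.

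The summed reading is never the more lenient one. If all 30 rate the item 4, E = 1.00 but S = 120/150 = 0.80, only just meeting the threshold.

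**The case against.** Asking once, straight after the intervention, is ordinary in a feasibility study. The form is qualitative and is to be analysed thematically. The Abstract names only exposure and responsiveness as success criteria. One missed session does not show dissatisfaction. All of this is fair: there is no numerical verdict on the form to overturn, and the absentees' views are unknown. But the Primary achievement goal section does count acceptability among the criteria of success, and a thematic analysis is as exposed to selective response as a percentage is.

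A reader might infer two stronger points, which the documents do not support.

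- **That the session-six form is judged against 0.80, so that absentees could turn a fail into a pass.** The form has open questions and yields no ratings of 4 or 5. The threshold is written for the satisfaction questionnaire, which appears to belong to the surveys at T0, T1 and T2. A student absent at session six can still answer at T1.
- **That half 5s and half 3s would pass on a summed score, (0.5 × 5 + 0.5 × 3)/5 = 0.80, while only 50% endorse.** This counts 3s, which the plan excludes. With only 4s and 5s counted, the sum is 0.5 × 5/5 = 0.50, equal to the share endorsing, and both readings fail.

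Scoring detail may also be left to a fuller document. What stands is that the one sentence printed here combines two quantities without a unit.

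**Conclusion.** The point holds for the primary acceptability form. As planned, it is not put to students absent from the sixth session or no longer attending, while the attendance criterion tolerates such absence and withdrawers' data are set aside. Upward bias is likely. If 4 of 25 or 5 of 30 are missing, it is at most 0.16 to 0.17 on a favourable share, and zero if absentees think as attenders do. This rests on the arm size of 25 to 30, on absence at session six equal to the low attendance tolerated, and on a favourable-or-not coding that the plan does not itself use. Absence could be larger or smaller.

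The 0.80 rule is a separate and secondary wording point. It concerns the satisfaction questionnaire, and the verdict can differ between readings (0.80 against 0.64 in the example). It does not follow that the satisfaction scale should become the primary acceptability measure; that would be a matter of preference.

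**What to change.** 1. In the acceptability section, offer the same open-question form to every student allocated to G-SS who has not withdrawn consent, including those absent from session six and those who stopped attending, by e-mail or with the T1 survey. Answering stays voluntary.
2. Report how many did not respond, with the number of sessions they attended. Keep the form descriptive.
3. Reconcile this with the withdrawal rule under Study setting and the intention-to-treat statement under Statistics, so that ceasing to attend and withdrawing consent are told apart and the use of data is clear for each.
4. Under Statistics, state that 0.80 applies to the satisfaction questionnaire, define it once as the share of item responses rated 4 or 5, and delete the word 'summation'.

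The cost is one extra mailing or survey page, wording changes in three sections, and a check that the revised text agrees with the participation terms. The small downside is later recall among those who were not present.

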##### Recruitment of retired physiotherapists

Retired physiotherapist should work as tutors with groups of six students. A total of five tutors will be recruited. Criteria of success will be set as 100% if five retired physiotherapists can be recruited.

#### Secondary achievement goals

These include the learning outcomes, satisfaction, self-efficacy, and students’ images of old age. Physical performance level of the retired physiotherapists and the G-SS implementation into the curriculum.

### Outcome measures

Students’ learning outcome

Students’ learning outcome could be defined as of what a learner is expected to know, understand or be able to do at the end of a period of learning (21). Learning outcome will be measured based on the semester exams (ordinal scaled) including written multiple-choice questions (MCQs) and an Objective Structured Clinical Examination (OSCE). The written exams consist of 87 single best answer MCQs. The OSCE consist of eight 8-min stations. The maximum score will be 87 and 64 points for the MCQs and OSCE, respectively. The exam will be passed if 60% of the total score is reached.Student’s satisfaction will be assessed with the student learning satisfaction questionnaire (22).Self-efficacy will be assessed using the self-efficacy learning (SEL) questionnaire (23).
Level of retired physiotherapists’ physical and cognitive performance. Physical performance capacity will be evaluated using the Short-Physical-Performance-Battery-Test while evaluation of the cognitive performance will be assessed using the Trail-Making A and B test before the start of the tutorship after the end of the first and second semester, respectively.Level of age images of physiotherapy students are assessed before the G-SS and F-SS lessons at the end of first and second semester, respectively. Age images will be assessed with the age images questionnaire (24).Level of G-SS curriculum implementation: the integration of G-SS into the existing curriculum will take place after evaluation of this planned feasibility study (i.e., after the second semester).

### Potential confounders

Education takes place in different social environments (e.g., classroom, mentoring where lecturers have an impact). Students may have different expectations regarding learning support by lecturers. As a result, this may affect learning gains during the first semester. In this case, classroom instruction mentoring will not be carried out in the first semester and lectures will take place according to the traditional teaching method. There are neither Moodle exercises nor preparatory assignments in the sense of a blended learning approach scheduled during the first semester.

### Covariates

Age, gender, local geographic matching, duration of school attendance and student cohort will be identified and recorded as possible covariates.

### Sample size

At the BFH-SHD bachelor’s degree course are always 102 bachelor students enrolled that will be allocated into two groups. We want to recruit five retired physiotherapists. Assuming the intra-cluster correlation coefficient (25) of 0.05 a design effect of 5.25 is given. Sample size is for this study 111.3 (612/5.25).

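### The printed sample size of 111.3 does not follow from its own inputs, rests on a design effect no cluster in the design can produce, and cannot be met by the enrolled cohort

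*Protocol article*

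**What the plan says.** The only sample-size calculation is in the Sample size section of the protocol article. It describes the pool as "always 102 bachelor students enrolled that will be allocated into two groups", plans for five tutors, and then concludes: "Assuming the intra-cluster correlation coefficient (25) of 0.05 a design effect of 5.25 is given. Sample size is for this study 111.3 (612/5.25". It does not say what 612 counts or which cluster size lies behind 5.25.

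Other sections bear on the same quantity:

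- Participants: "The objective is to recruit a minimum of 30 first-semester physiotherapy students from the BFH-SHP (17". This minimum is also an a priori criterion of recruitment success.
- Intervention program: "Students of the G-SS will be divided into five groups of five to six students each".
- Eligibility criteria and Participants: students repeating the first semester, and students who do not wish to take part, are left out.
- Allocation concealment: students are placed in groups A, B, C or D. One coin toss then decides whether A/B or C/D receives G-SS.
- Control condition: the free self-study (F-SS) arm has no tutoring.
- Statistics: testing intervention effects is not a key part of the design.

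**The concern.** Inputs, formula and result all stand in one short paragraph, so a reader can check them at once, and they do not agree. The quotient is not the result of the division shown. The design effect is far above what an intra-cluster correlation of 0.05 gives for small tutor groups. The result is also larger than the number of students the same paragraph says exist.

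At stake is whether the reader can tell how many students the study means to include and on what basis. As printed, the paragraph offers a precise figure that can be neither derived nor reached.

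**Working it through.** **Inputs.** From Sample size: 102 students, five tutors, intra-cluster correlation 0.05, design effect 5.25, numerator 612, result 111.3. From Intervention program: five G-SS groups of 5 to 6, hence 5 × 5 = 25 to 5 × 6 = 30 places. From Allocation concealment: four groups, paired into two blocks. Assumption: the 102 are split equally, giving about 102/4 = 25.5 per group and 102/2 = 51 per block.

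**1. The plan's own figure.**
- 612/5.25 = 116.57, not 111.3. The gap is 5.3 students, or 4.7% of 111.3, too large for rounding.
- 612/111.3 = 5.499, and 612/5.5 = 111.27. The printed result therefore belongs to a divisor of 5.5.

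**2. The design effect.** With equal clusters of size m, design effect = 1 + (m − 1) × 0.05.

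| Cluster | m | Design effect |
|---|---|---|
| Tutor group | 5 | 1.20 |
| Tutor group | 6 | 1.25 |
| One of groups A to D | 25 to 25.5 | 2.20 to 2.23 |
| Randomised block | 51 | 3.50 |
| Whole cohort as one cluster | 102 | 6.05 |

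Solving backwards:
- 5.25 needs m = 1 + 4.25/0.05 = 86.
- 5.5 needs m = 1 + 4.5/0.05 = 91.

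The protocol describes no cluster of either size. The printed 5.25 is 5.25/1.25 = 4.2 times the value for tutor groups of six, but only 5.25/3.5 = 1.5 times the value for a randomised block.

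**3. Can the result be a head-count?** 111.3 exceeds 102 by 9.3, and 116.6 exceeds it by 14.6. This is before repeaters and non-consenters are removed.

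**4. Can it be an effective sample size?** Dividing an actual count by the design effect does give an effective size. The actual count would then be 612, six times the 102 enrolled. The text also presents 111.3 as the sample size for the study, not as an effective size.

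**5. Comparison with the other stated sizes.** A study of 111.3 in two equal arms would have about 55.7 per arm, and the full cohort would have 51. The tutor groups hold 25 to 30. Participants asks for at least 30 without saying whether that counts both arms or only G-SS. No text links these numbers.

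A correct required size cannot be computed instead: the paragraph gives no effect size, variability or power, and 612 has no stated basis.

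**The case against.** Several points on the other side are fair.

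- **Direction of the operation.** A reader might infer that dividing by the design effect is itself a mistake, since a required individually randomised size is multiplied by it (612 × 5.25 = 3213). The text does not settle this. Division is the right operation for an effective size, and the paragraph does not say which quantity it reports. What stands is that neither reading works.
- **The number 612.** It equals 6 × 102, but what it represents would be a guess. An article condensing a fuller protocol may leave its source there. The missing explanation alone shows no error.
- **The minimum of 30.** A reader might see a flat contradiction with 111.3. A floor for recruitment success can coexist with a larger planned size. What stands is that the two are not reconciled.
- **Damage to the main study.** A reader might infer that the design effect will mis-size the main study about four-fold. That takes the smallest cluster as comparator; against the randomised block the ratio is 1.5. The figure is given for this study, and nothing shows it will be reused.
- **A ready replacement.** It is tempting to substitute 1.25 and an effective size of 102/1.25 = 81.6. That would apply tutor clustering to a control arm without tutors, and to 102 students when the tutor groups hold 25 to 30. It would also ignore the blocks that are actually randomised.
- **Little depends on it.** The Statistics section plays down effect testing. The criteria on attendance, session length, acceptability and recruitment do not use 612, 5.25 or 111.3. This limits the consequence but does not make the paragraph correct.

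**Conclusion.** The point holds as an error in the printed calculation. Three parts are firm: the quotient is off by 5.3 (116.6 against 111.3), the design effect of 5.25 matches no cluster in the design at the stated correlation, and the result fails both as a head-count (above 102) and as an effective size (612 students needed). The lack of any link to the minimum of 30 and the 25 to 30 G-SS places leaves the intended size unclear, but is not a contradiction in itself.

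This rests on the standard design-effect formula with equal clusters, on 102 being the pool to be allocated, and on an equal split for the values 2.2 and 3.5. The capacity of 25 to 30 uses the five tutors planned in the Sample size section; the Discussion speaks of six. The division error needs none of these assumptions. The documents do not support going further, to a proven error of direction or a four-fold mis-sizing of the main study. The feasibility conclusions do not depend on the wrong figures.

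**What to change.** Rewrite the Sample size paragraph:

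1. Delete 612, 5.25 and 111.3.
2. State that the size is fixed by the cohort (at most 102 students, less repeaters and non-consenters) and by tutor capacity (25 to 30 G-SS students with five tutors).
3. Say how the minimum of 30 in Participants relates to this, including whether it counts both arms or only G-SS.
4. If a design effect is kept, compute it as 1 + (m − 1) × 0.05 and name the cluster level that m refers to. Note that tutor-group clustering exists only in the G-SS arm, and that one coin toss between two blocks leaves one randomised unit per arm, so no design effect by itself separates the intervention from differences between the blocks.

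The cost is one reworded paragraph. It needs no extra students and no change to the feasibility criteria.
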